# A phase II trial comparing pazopanib with doxorubicin as first-line treatment in elderly patients with metastatic or advanced soft tissue sarcoma (EPAZ): study protocol for a randomized controlled trial

**DOI:** 10.1186/s13063-016-1434-x

**Published:** 2016-07-07

**Keywords:** Soft tissue sarcoma, Elderly, Doxorubicin, Pazopanib, Noninferiority

## Abstract

**Background:**

Anthracycline-based treatment remains the backbone of chemotherapy for nonresectable soft tissue sarcomas (STS). More than 30 % of patients with STS are aged 60 years or older, limiting the choice of treatment to single-agent approaches for this elderly population. Hematological toxicity is frequent during doxorubicin monotherapy, grade 4 neutropenia is reported in 34 %, with a febrile neutropenia rate of 9 % in STS. We assume that comorbidities in the elderly population may limit tolerability of doxorubicin, and novel agents may improve tolerability and health-related quality of life while maintaining efficacy. We therefore investigated whether the tyrosine kinase inhibitor pazopanib exerts such a clinical benefit in elderly patients with STS (pazopanib for elderly [the EPAZ study]).

**Methods/design:**

This study is a randomized, controlled, open-label, multicenter, phase II noninferiority trial in which pazopanib 800 mg once daily is being compared six cycles of intravenous doxorubicin 75 mg/m^2^ as first-line treatment in elderly patients (≥60 years) with metastatic or advanced STS. A total of 120 patients will be randomized 1:2 to receive doxorubicin or pazopanib, stratified by Eastern Cooperative Oncology Group performance status (0–1 vs. 2) and liposarcoma histology (yes vs. no).

The primary endpoint is progression-free survival based on local tumor assessment according to Response Evaluation Criteria in Solid Tumors criteria. Secondary endpoints include grade 4 neutropenia and febrile neutropenia in hierarchical order, as well as overall survival, objective response rate, health-related quality of life, and geriatric assessments.

**Discussion:**

Pazopanib is associated with promising tolerability according to previous studies and may offer a significant clinical advantage in first-line treatment of STS compared with doxorubicin. The elderly population seems especially appealing for such an approach, since these patients are not suitable for aggressive combination therapy. The EPAZ study will confirm whether pazopanib may be an alternative to toxic chemotherapy for elderly patients with STS.

**Trial registration:**

ClinicalTrials.gov NCT01861951; registered on 11 April 2013. EudraCT 2011-004168-30; registered on 4 June 2012.

**Electronic supplementary material:**

The online version of this article (doi:10.1186/s13063-016-1434-x) contains supplementary material, which is available to authorized users.

## Background

Soft tissue sarcomas (STS) are malignant, heterogeneous tumors that typically arise in the mesodermal tissues of the extremities (50 %), trunk and retroperitoneum (40 %), or head and neck (10 %) [1]. Their histology is diverse, and more than 50 different subtypes are recognized in the current classification system [2].

STS in adults are rare and have an estimated incidence of 4–5 per 100,000 per year in Europe [3]. In the United States, more than 10,000 new cases were reported in 2010 [4]. The aggressiveness of STS is emphasized by the high death rate, with nearly 4000 deaths occurring in the United States in 2010. Risk factors for recurrent disease are described as incomplete resection, high-grade histology, STS larger than 5 cm, and deep location [5].

As a result of STS heterogeneity, the development of an effective antitumor agent has been difficult. For decades, doxorubicin has formed the backbone of systemic treatment of a wide range of cancers, including hematological malignancies, many types of carcinoma, and unresectable or metastatic STS [6]. Doxorubicin treatment is frequently associated with hematological toxicity. Grade 4 neutropenia has been reported in 34–37 % of patients with STS during treatment with doxorubicin, and 9–13 % of all patients being treated with doxorubicin experience febrile neutropenia [7, 8].

Elderly patients are known to be prone to comorbidities, and aggressive treatment may not be feasible for these patients, which is why multiagent chemotherapy is not recommended for them. However, grade 4 neutropenia and neutropenic fever are considered severe side effects of palliative treatment and may be poorly tolerated by elderly patients. Finding an alternative agent with similar efficacy but fewer and less severe adverse effects (AEs) is therefore particularly important for this patient group.

A promising candidate for this purpose could be pazopanib, which is an orally administered, potent, multitargeted receptor tyrosine kinase inhibitor. Pazopanib has demonstrated encouraging results in clinical trials in renal cell carcinoma, ovarian cancer, early-stage non-small cell lung cancer, breast cancer, and cervical cancer [9–14]. In a phase II study of patients with advanced or metastatic STS receiving pazopanib as a second-line therapy, the progression-free rate (PFR) at 12 weeks was 44 % (18 of 41 subjects) for leiomyosarcoma, 49 % (18 of 37 subjects) for synovial sarcoma, 26 % (5 of 19) for adipocytic sarcoma, and 39 % (16 of 41 subjects) for other types of sarcoma [15]. Agents with a PFR of at least 40 % at 12 weeks are suggested to show adequate drug activity in pretreated patients [16]. Therefore, further clinical development of pazopanib excluded patients with adipocytic sarcoma from clinical trials after the given phase II results. The PALETTE (pazopanib for metastatic soft-tissue sarcoma) study investigators assessed pazopanib in comparison with placebo in STS excluding adipocytic differentiation [17]. Pazopanib achieved a significant improvement in median progression-free survival (PFS) from 1.6 to 4.6 months (*p* < 0.0001), which was the primary endpoint of the trial. Overall survival increased from 10.7 to 12.5 months (HR 0.86, 95 % CI 0.7–1.1; *p* = 0.25), but the study size was too small to detect such a treatment effect.

Overall, pazopanib offers a distinct mechanism of action and spectrum of adverse events, thereby offering some advantage over conventional chemotherapy. In our present study, we are testing this hypothesis in comparison with single-agent doxorubicin in elderly patients with STS.

## Methods

### Study objectives

The primary aim of this study is to show that PFS in the pazopanib group is not inferior to PFS in the doxorubicin group. Key secondary objectives are to show superiority of pazopanib compared with doxorubicin regarding neutropenia grade 4 and/or febrile neutropenia. Further secondary objectives are to analyze treatment effects on overall survival, objective tumor response, time to onset of response, quality of life, safety, and tolerability, as well as to investigate predictive biomarkers.

### Study design

This trial is a randomized, open-label, multicenter, phase II noninferiority study designed to compare pazopanib with doxorubicin as first-line treatment in elderly patients with metastatic or advanced STS. A total of 120 patients from 13 (German and Belgian) study centers will be enrolled, comprising 40 patients in the doxorubicin arm and 80 patients who will receive pazopanib.

The overall study duration will be approximately 50 months, including a recruitment period of 36 months, a 4.5-month period of treatment with doxorubicin (18 weeks) or pazopanib until treatment failure, and follow-up of at least 10 months.

Baseline and follow-up assessments are performed according to a predefined schedule (see Fig. 1 and Additional file 1: Figure S1). Follow-up visits occur at the same time points for both treatment arms. In both treatment groups, an end-of-treatment visit 4 weeks after the end of treatment is performed. Tumor images obtained by performing computed tomography or magnetic resonance imaging for evaluation of response and progress are taken every 6–7 weeks in the first 6 months and every 12 weeks after week 26 until progression. The Standard Protocol Items: Recommendations for Interventional Trials (SPIRIT) checklist and assessment figure of the trial can be found in Additional file 2: Table S1 and Additional file 1: Figure S1.

**Fig. 1 Fig1:**
[figure not shown]
Schedule of visits and treatment. *RECIST* Response Evaluation Criteria in Solid Tumors

### Ethical considerations

The trial protocol was approved by the ethics committee of Hannover Medical School and the ethics committees of all participating study centers (see Additional file 3). The study is registered at ClinicalTrials.gov (identifier NCT01861951) and ClinicalTrialsRegister.eu (identifier 2011-004168-30). The results of the trial will be reported in accordance with the Consolidated Standards of Reporting Trials (CONSORT) statement [18, 19].

### Study population

Male and female patients with metastatic or advanced STS who are at least 60 years of age are screened for the study. After they provide signed written informed consent, their eligibility is determined on the basis of the inclusion and exclusion criteria listed in Table 1.

**Table 1 Tab1:** Inclusion and exclusion criteria

Inclusion criteria	Exclusion criteria
• Signed written informed consent	• STS of uncertain differentiation (epithelioid, alveolar soft part, clear cell, desmoplastic small round cell, malignant mesenchymoma, PEComa), chondrosarcoma, Ewing sarcoma/PNET, chordoma, malignant solitary fibrous tumors, embryonal rhabdomyosarcoma, osteosarcoma, gastrointestinal stromal tumors, dermatofibrosarcoma protuberans, inflammatory myofibroblastic sarcoma (low grade), neuroblastoma, malignant mesothelioma, mixed mesodermal tumors of the uterus
• Age ≥60 years	• Prior malignancy, except for subjects who have been disease-free for 2 years, or complete resection of nonmelanomatous skin carcinoma, or successfully treated in situ carcinoma or incidental prostate cancer (TNM stage T1a or T1b)
• ECOG performance status of 0–2	• History or clinical evidence of CNS metastases; previously treated subjects without signs of activity are allowed
• Histologically confirmed diagnosis of metastatic or advanced STS of intermediate or high grade	• Clinically significant gastrointestinal abnormalities that may increase the risk for gastrointestinal bleeding or may affect absorption of IMP
• Evidence of progressive disease within 6 months prior to study inclusion	• Presence of uncontrolled infection
• Availability of archived tumor tissue of the most recent histology	• QTc >480 milliseconds using Bazett’s formula
• Adequate organ system function as determined by laboratory assessment	• History of any of the following cardiovascular conditions within the past 6 months: cardiac angioplasty or stenting, myocardial infarction, unstable angina, coronary artery bypass graft surgery, symptomatic peripheral vascular disease, cerebrovascular accident (including TIA), pulmonary embolism, or untreated deep vein thrombosis
• Adequate contraception for patients or partners with childbearing potential	• Class III or IV congestive heart failure as defined by the NYHA classification system
• Negative pregnancy test for women of childbearing potential	• Poorly controlled hypertension
	• Major surgery or trauma within 28 days before first dose of IMP and/or presence of any nonhealing wound, fracture, or ulcer
	• Evidence of active bleeding or bleeding diathesis
	• Known endobronchial lesions and/or lesions infiltrating major pulmonary vessels
	• Hemoptysis in excess of 2.5 ml once within 8 weeks of first dose of IMP
	• Any serious and/or unstable preexisting medical, psychiatric, or other condition that could interfere with subject’s safety, provision of informed consent, or compliance with study procedures
	• Unable or unwilling to discontinue use of prohibited medications for at least 14 days or 5 half-lives of a drug (whichever is longer) prior to the first dose of IMP and for the duration of the study
	• Treatment with any anticancer therapies
	• Any ongoing toxicity from prior anticancer therapy that is higher than CTCAE grade 1 and/or that is progressing in severity, except alopecia
	• Prior systemic therapy for metastatic or advanced disease; neoadjuvant or adjuvant chemotherapy is allowed, unless disease progression occurred within 6 months following end of treatment
	• Participation in any other clinical trial within 30 days before the study begins
	• Known hypersensitivity to any component of IMPs

*Abbreviations: CTCAE* Common Terminology Criteria for Adverse Events, *ECOG* Eastern Cooperative Oncology Group, *IMP* investigational medical product, *NYHA* New York Heart Association, *PEComa* perivascular epithelioid cell tumor, *PNET* primitive neuroectodermal tumor, *QTc* corrected QT interval, *STS* soft tissue sarcomas, *TIA* transient ischemic attack

### Randomization and blinding

This is an open-label study with a 1:2 randomization ratio for doxorubicin/pazopanib. Blinding was considered to be ethically infeasible due to the different dosing schedules and routes of administration. A fax randomization is centrally performed at the Institute for Biostatistics in Hannover according to a permuted block randomization list with varying block sizes. Randomization is stratified for Eastern Cooperative Oncology Group (ECOG) performance status (0–1 vs. 2) and liposarcoma histology (yes vs. no) at randomization.

### Interventions

#### Control intervention

Doxorubicin is an anthracycline antibiotic with a mechanism of action aimed at topoisomerase inhibition. Doxorubicin (monotherapy) is administered intravenously every 3 weeks at a dose of 75 mg/m^2^ body surface area for a total of six cycles.

#### Experimental intervention

Pazopanib is a once-daily, orally administered angiogenesis inhibitor targeting vascular endothelial growth factor (VEGF), platelet-derived growth factor, and c-kit receptors [20]. By inhibiting these receptors, pazopanib may stop or slow the rate of tumor growth and development. Pazopanib is provided as white tablets with two doses at 200 mg and 400 mg. Patients receive a daily dose of 800 mg. Treatment is administered until disease progression, treatment failure, or death due to any cause, whichever occurs first. Pazopanib has been approved by the U.S. Food and Drug Administration, the European Medicines Agency, and other regulatory authorities as a monotherapy for patients with advanced renal cell carcinoma and as second-line therapy for advanced STS.

#### Dose adjustments

Dose reduction, delay of administration, and treatment interruption might become necessary for reasons of toxicity in both treatment groups. Patients with dose adjustments are closely monitored (weekly). Dose modification algorithms are given in the study protocol. As a general rule, pazopanib is reduced stepwise each 10–14 days in 200-mg decrements. If the toxicity has abated with dose reduction and dose re-escalation is considered safe by the investigator, the pazopanib dose is increased stepwise back to the pre-event dose. For doxorubicin, a 1-week treatment delay and/or a 20 % dose reduction (i.e., 60 mg/m^2^) are suggested. Dose modifications to 60 mg/m^2^ doxorubicin are allowed once and cannot be re-escalated. If toxicity does not abate during the monitoring period, administration of pazopanib or doxorubicin is interrupted and/or the dose is further reduced. It should be permanently discontinued for any hematological or nonhematological toxicity requiring an interruption of ≥14 days.

### Outcomes

#### Primary endpoint

The primary endpoint is PFS, calculated as time from the date of randomization until the date of first objective documentation of disease progression, treatment failure, or death due to any cause, whichever occurs first.

#### Secondary endpoints

Key secondary outcomes are the rates of grade 4 neutropenia and of febrile neutropenia. Rates are defined as the number of scheduled examinations where grade 4 neutropenia is diagnosed (febrile neutropenia respectively) divided by the follow-up time until progression, death, or the end of the study, or (in case of treatment switch) until initiation of another anticancer treatment. Incident diagnoses will be considered at the next examination. In addition to the primary outcome, PFRs after 12 and 26 weeks from the date of randomization and overall survival, defined as time from randomization to death due to any cause, will be estimated. Further secondary endpoints are objective tumor response, calculated as objective response rate, along with time to onset of response. Assessment of response and progression is based on Response Evaluation Criteria in Solid Tumors version 1.1, without independent review of tumor response or progression events.

Safety and tolerability will be assessed continuously throughout the course of the study. Toxic and side effects are evaluated by using the National Cancer Institute Common Terminology Criteria for Adverse Events version 4.0. Quality of life is measured with the European Organisation for Research and Treatment of Cancer (EORTC) 30-item core quality of life questionnaire (the QLQ-C30). Geriatric assessments are made according to the EORTC Elderly Task Force guidelines.

The predictive role of biomarkers will be assessed to predict the PFS rate at 26 weeks after the start of treatment. Biomarkers measured in the study will include placental growth factor, fibroblast growth factor, VEGF, PDGF, angiopoietin 2, and interleukin 8. Blood samples will be taken at baseline, at 2 weeks, and at each scheduled follow-up visit starting from 3 weeks after randomization.

#### Further assessments

A large panel of clinical and laboratory data is being collected in the trial. At each visit, a physical examination is conducted, including assessment of vital signs, and information on hematology and clinical chemistry is obtained, which are particularly important for assessment of tolerability. Evaluation furthermore comprises liver function tests, coagulation tests, proteinuria via urinalysis, thyroid function tests, and lipid tests. Echocardiography is performed at baseline and at week 26. Based on the key secondary endpoints, primary and secondary prophylaxis of neutropenia assessment is of key importance. Primary and secondary prophylaxis of neutropenia are routinely assessed and documented for each cycle. The participating trial centers have decided at baseline whether they will implement primary prophylaxis.

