#### Secondary and safety analyses

If statistical significance is reached for the primary endpoint, a confirmatory analysis of the key secondary endpoints grade 4 neutropenia and febrile neutropenia will be performed in hierarchical order. If no statistically significant difference for grade 4 neutropenia is observed, febrile neutropenia will be considered descriptively. The rates of grade 4 neutropenia will be analyzed with a Poisson regression model adjusted for ECOG score and liposarcoma histology and allowing for clustering of the outcome within patients by using a random effects term. Superiority of pazopanib will be concluded if the upper boundary of the two-sided 95 % CI for the rate ratio (pazopanib/doxorubicin) is below 1. Rates of febrile neutropenia will be analyzed with the same approach. Due to the hierarchical order in confirmatory testing, no adjustment for multiplicity has to be done.

For the analysis of overall survival, Kaplan-Meier curves and Cox regression will be used. For analysis of PFRs after 12 and 26 weeks, a logistic regression model will be used to calculate the OR between the two treatment groups. Corresponding two-sided 95 % CIs will be calculated. The objective tumor response rate will be computed with 95 % CIs in each treatment arm. Patients with progression, early death, or unknown status are considered as failures. Time to onset of response will be reported as median and range. Occurrence and frequency of AEs and serious AEs will be evaluated separately for both treatment groups, and frequency tables and corresponding 95 % CIs will be shown.

The key secondary analyses and analyses of all further efficacy endpoints will be conducted on the ITT population with sensitivity analyses based on the PP population. Analysis of safety endpoints will be conducted on the full analysis set. No interim analyses are planned in this trial.

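### The confirmatory neutropenia models leave out each center's baseline primary prophylaxis policy, so chance imbalance goes uncorrected and any dependence of the ratio on center mix stays hidden

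*Protocol article*

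**What the plan says.** The Further assessments section of the Protocol article gives prophylaxis a special place: "Based on the key secondary endpoints, primary and secondary prophylaxis of neutropenia assessment is of key importance". It adds: "Primary and secondary prophylaxis of neutropenia are routinely assessed and documented for each cycle". It then describes a center-level decision: "The participating trial centers have decided at baseline whether they will implement primary prophylaxis".

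The design and analysis sections do not use that decision. Under Randomization and blinding: "Randomization is stratified for Eastern Cooperative Oncology Group (ECOG) performance status (0–1 vs. 2) and liposarcoma histology (yes vs. no) at randomization". Under Secondary and safety analyses, grade 4 neutropenia is to be "analyzed with a Poisson regression model adjusted for ECOG score and liposarcoma histology and allowing for clustering of the outcome within patients", the clustering being handled by a random effect. For the second key endpoint: "Rates of febrile neutropenia will be analyzed with the same approach". Superiority is concluded if the upper 95% limit of the rate ratio (pazopanib/doxorubicin) is below 1. The Discussion again names only ECOG status and liposarcoma histology as factors for stratified randomization and analysis.

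**The concern.** The article identifies a factor that bears on the confirmatory endpoints, says it was settled by center at baseline, and then specifies models without it. The covariate set is stated, so the point questions a stated choice and does not report a detail left to the analysis plan.

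Two things are at stake. First, neither center nor policy is balanced by design, so with 40 against 80 patients the arms can differ by chance in the share treated at prophylaxis centers. Second, if prophylaxis changes the doxorubicin rate more than the pazopanib rate, the single pooled ratio is an average whose value depends on how many patients came from each type of center.

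The endpoints matter to the trial's message. The Discussion concedes that the margin of 1.8 allows a loss of progression-free survival from 6 to 3.3 months, which it regards as clinically unacceptable, and it gives the neutropenia endpoints weight partly for that reason.

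**Working it through.** **The plan's own figure.** No power is stated for the neutropenia endpoints. The only power figure concerns progression-free survival. With exponential times, median 6 months, 36 months' accrual and 10 months' minimum follow-up, the event probability is 0.925. That gives 111.1 events from 120 patients and 99.9 from 108. Power for margin 1.8 at one-sided 2.5% and 1:2 allocation is 83.1% and 79.1%, against the stated >80% and 79–80%. It reproduces, and the present point does not touch it.

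**Inputs.** From the article: 40 doxorubicin and 80 pazopanib patients, 13 centers, and the stated model. Assumed, because the article gives no values: the share s of patients at prophylaxis centers, the factor f by which prophylaxis multiplies the neutropenia rate, and the ratio r0 without prophylaxis. Equal follow-up and simple 40:80 allocation are also assumed.

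**1. Chance imbalance.** Take s = 50%, that is 60 of 120 patients. The number X of these in the doxorubicin arm is hypergeometric, with variance 40 × 0.5 × 0.5 × 80/119 = 6.72 and SD 2.59.
- The arm difference in share is X/40 − (60 − X)/80, with SD 2.59 × 3/80 = 9.7 points.
- The chance of a difference of at least 10 points is 33%, and of at least 15 points 17%.
- At s = 25% or 75% the SD is 8.4 points and these chances are 26% and 12%.

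**2. Same effect in both arms.** The unadjusted ratio is multiplied by [1 − (1 − f)·s_paz] / [1 − (1 − f)·s_dox], where s_paz and s_dox are the shares in the two arms. The 95% range of X is 15 to 25. For f = 0.5:
- X = 15: (1 − 0.5 × 0.5625)/(1 − 0.5 × 0.375) = 0.71875/0.8125 = 0.885
- X = 25: (1 − 0.5 × 0.4375)/(1 − 0.5 × 0.625) = 0.78125/0.6875 = 1.136

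For f = 0.3 the range is 0.822 to 1.233; for f = 0.7 it is 0.937 to 1.069. In this scenario the true ratio does not depend on center mix.

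**3. Effect on doxorubicin only.** The pooled ratio is r0/(1 − s + s·f). With r0 = 0.30:

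| f | s = 0% | 25% | 50% | 75% | 100% |
|---|---|---|---|---|---|
| 0.7 | 0.30 | 0.32 | 0.35 | 0.39 | 0.43 |
| 0.5 | 0.30 | 0.34 | 0.40 | 0.48 | 0.60 |
| 0.3 | 0.30 | 0.36 | 0.46 | 0.63 | 1.00 |

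Chance imbalance matters less here, because only the doxorubicin arm's own share counts (SD 2.59/40 = 6.5 points). For f = 0.5 and X from 15 to 25 the factor runs from 0.75/0.8125 = 0.92 to 0.75/0.6875 = 1.09.

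**4. What a main-effect covariate buys.** Simulation with 13 centers, gamma frailty, 1.0 event per doxorubicin patient without prophylaxis, r0 = 0.30 and f = 0.4. A Poisson model with robust standard errors stands in for the random-effects model. Entries are median ratio and chance of concluding superiority:

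| Prophylaxis acts on | Share of centers | Without policy | With policy |
|---|---|---|---|
| both arms | 25% | 0.30; 92.9% | 0.30; 93.4% |
| both arms | 50% | 0.30; 88.2% | 0.30; 90.1% |
| both arms | 75% | 0.30; 81.0% | 0.30; 83.2% |
| doxorubicin only | 25% | 0.35; 86.4% | 0.35; 86.8% |
| doxorubicin only | 50% | 0.42; 70.9% | 0.42; 71.9% |
| doxorubicin only | 75% | 0.57; 35.4% | 0.57; 35.5% |

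With a true ratio of 1 and the common factor, the unadjusted model concluded superiority in 2.2% to 3.5% of runs and the adjusted model in 3.0% to 3.7%.

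**The case against.** The strongest defense is that validity is untouched. A policy fixed before allocation cannot bias a randomized comparison in expectation, the simulated error rate is no worse without the covariate, and adjusting for exactly the stratification factors is a standard choice. The precision argument is also weak, since the gain is about 0.5 to 2 points of power at most. All of this stands.

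The inputs are assumptions too. The article gives no prophylaxis effect, no share of centers and no statement that the effect differs by arm. A doxorubicin-specific effect is a natural reading, because prophylaxis is documented per cycle and doxorubicin is the arm given in cycles, but it remains an inference.

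Three stronger readings are tempting and not supported:
- A reader might infer that the pooled ratio has no meaning for either practice. An average effect under local supportive care is a legitimate quantity in a multicenter trial; it is only incomplete if the effect differs by policy.
- A reader might take the Background's 34–37% as the doxorubicin rate without prophylaxis. The article does not say whether those patients received it. The figure is also a proportion of patients, whereas the endpoint counts positive scheduled examinations over follow-up time.
- A reader might add the 9.7-point imbalance to the mix dependence. They belong to different scenarios: the full arm difference counts when prophylaxis acts in both arms alike, and the mix matters when it does not.

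Tables by prophylaxis may well be in an analysis plan that is not shown. That does not answer the point about the stated covariates. The endpoints are also second in the hierarchy and, as the Discussion says, unpowered, which limits the weight of the point.

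**Conclusion.** The point holds as a moderate weakness of the stated analysis, not as a flaw in its validity. The models omit a center-level factor that the article itself links to the endpoints, and chance imbalance in it is therefore left uncorrected. At an assumed 50% share and a halving in both arms, this moves the ratio by 0.885 to 1.136 (95% range). Under a doxorubicin-only effect the imbalance matters less (0.92 to 1.09), but the pooled ratio then shifts with the center mix: 0.30, 0.40 or 0.60 at 0, 50 or 100% of patients at prophylaxis centers, assuming 0.30 without prophylaxis and a halving. Adding the covariate does not remove that shift; only results by policy show it. The conclusion also rests on reading the centers' decision as made before their patients were allocated, which should be confirmed.

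**What to change.** Before analysis, add the center's baseline primary prophylaxis policy (yes/no) to the grade 4 neutropenia model, and to the febrile neutropenia model if event numbers allow a stable fit. Use the policy, not the prophylaxis actually given, because actual use follows randomization in an open-label trial. The article documents prophylaxis per cycle but does not say that policy is held as a variable, so it may have to be taken from center records.

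Report grade 4 neutropenia rates and the rate ratio by policy descriptively, or through a supportive model with a treatment-by-policy term, and leave the superiority rule on the covariate-adjusted ratio. Recruitment is complete, so stratification cannot change; with follow-up ongoing at publication, the analysis still could.

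The cost is one parameter and one table, for a small gain in power. The stratum estimates will be imprecise, with about 20 doxorubicin patients each at an even split. For febrile neutropenia, the Background's 9–13% applied to 40 patients gives only 3.6 to 5.2 doxorubicin patients with an event in total, too few for results by policy.
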